### Intervention Group

The participants were able to learn about the study through social media, advocacy organizations, and word-of-mouth. A researcher, along with a sign language interpreter, contacts each potential participant through a WhatsApp video call (the key communication channel among Deaf organizations in Colombia, using sign language) to explain the project and schedule a medical appointment. Upon arrival at the hospital, participants are greeted by a research assistant who facilitates their admission process. The participants were then guided to the consultation room.

The participants engage in a standard medical consultation known in the Colombian health system as “standard promotion and disease prevention or annual check” using VRI as the means of communication. During the consultations, the health care professional conducts a medical history assessment, performs a physical examination, and provides education and recommendations based on the findings.

The VRI is used during the appointment. A 32-inch screen displays the Colombian Sign Language interpreter, who connects through the Zoom (Zoom Video Communications) platform. A professionally accredited Colombian Sign Language interpreter with robust experience in medical interpretation facilitates communication between the health care professional and the Deaf participant during the consultation.

After the medical consultation, participants complete the Doctor-Patient Communication (DPC) scale. This scale is administered by a research assistant using a tablet and is available on the LimeSurvey platform with Spanish subtitles and Colombian Sign Language videos.

### Control Group

The participants in the control group gain access to the same intervention, albeit without VRI contact. They communicate with the doctor using standard communication methods (eg, self-arranging interpretation, lip-reading, note-taking, or the use of images).

### Explanation for Choice of Comparator

In-person or VRI sign language interpretation is largely unavailable. Thus, there are no clear data on the magnitude of the availability gap of VRI or in-person interpretation. In-person qualified sign language interpretation in the health care setting is considered the ideal service provision standard. Thus, it is mainly unavailable even in HICs. Furthermore, the assumption is based upon minimal available evidence on the personal preferences of Deaf people in the United States. There is no evidence that in-person interpretation is efficient in the context of weaker regulation and infrastructure, such as low sign language proficiency rates among Deaf people, lack of standard qualification of interpreters, and lack of interpreters and sustainable financing. To our knowledge, no study assesses DPC while using sign language interpretation.

Given the cost, VRI may be more sustainable than in-person care. Given that there is no other effective intervention to compare, assessing the efficiency of VRI versus the standard of care would be of greater value.

### Sample Size

This study includes 216 participants who were randomized into 2 groups. As no clinical trials in the field have been undertaken, there are no previous effect sizes to consider. However, 216 participants are deemed sufficient to find clinically significant differences.

To establish that the control group that uses VRI improves concerning the variables of interest, we followed the superiority approach and computed the sample size needed using the equation given below:

Where Zα=1.64 is the *z* score considering the level of significance to be 5%, α =.05; Zβ=0.84 is the *z* score for 80% power, β = 0.2; δ=0.05 is the superiority margin (5%); p1=0.85 is the proportion in the intervention group; p2=0.65 is the proportion in the control group; d=p1–p2 is the difference between the true groups, which is 0.20; r=1 is the ratio of the sizes of the 2 groups (considering the same size for both the groups); and n is approximately 97.

Consequently, under these conditions, we expect 10% of the enrolled participants to drop out due to any circumstances that may arise and therefore not be analyzable. The final sample size was 100×(2n)/(100–10), about 216.

### Inclusion, Exclusion, and Withdrawal Criteria

#### Inclusion criteria

To be included in the study, the participants must reside in Bogotá, Colombia, be aged at least 18 years, be fluent in Colombian Sign Language, and have the availability to attend the medical appointment. In addition, they must possess sufficient sensorimotor, cognitive, and communication skills to interact with health care personnel independently.

#### Exclusion criteria

Participants are excluded if they have additional impairments that affect language development or the use of sign language.

#### Withdrawal

Participation can be withdrawn during the treatment period without specifying a reason behind the decision.

### Safety Monitoring and Reporting

The study has been registered in ClinicalTrials.gov under the identifier NCT05966623 since November 29, 2023. The data being stored will be encrypted, and all participants will receive an identification code, thus ensuring the anonymity of the participants during the analysis of the results. The LimeSurvey website is publicly accessible and allows for a wider distribution of surveys. The University of Geneva and Universidad del Rosario, partners in this research, are institutionally subscribed to this platform. The service provided by the platform meets the data protection and security requirements mandated by the relevant legal frameworks and ethical standards in Colombia and Switzerland. Furthermore, the transfer and storage of data comply with security guidelines. Access to the collected data is strictly restricted to research team members.

### Assignment of Interventions: Blinding

To prevent selection bias, the participants will be assigned to the intervention or control group using random assignment techniques with block randomization. The randomization of participants will allow for the evaluation of treatment effects while ensuring that the observed outcomes are truly due to the treatment and not influenced by other factors. Using blocks in random assignment is a common strategy to ensure that the groups are balanced in terms of relevant characteristics, which helps minimize variability and potential biases in assigning patients to the study groups. In this case, a randomization list will be created using the website randomization.com. This site will facilitate random assignments using the block method to ensure a balanced allocation of patients between the 2 groups.

A defined procedure will be followed to define the block randomization lists.

First, determining the block size: a block size of 4 will be defined (2 patients for each group). This block size is chosen because it is a multiple of the number of groups, which in this case are 2 (intervention and control). Having a block size that is a multiple of the number of groups ensures that each group is equally represented within the blocks, which aids in maintaining a balanced random assignment of patients to the intervention and control groups. This helps ensure the validity and reliability of the study results.

Second, randomly assigning each participant within a block to a group: for example, with a block size of 4 and 2 groups (control and intervention, A and B), the assignment could be as follows:

Block 1: ABBABlock 2: BAABBlock 3: ABABBlock 4: BABA

This process continues until all participants have been assigned to the different groups. To maintain concealment, the block sizes will not be revealed.

Once the participants enter the medical appointment, they will receive a box containing several envelopes. Each participant will select an envelope that will provide their participant code and the corresponding group designation (control or intervention). The researcher, the participant, the general practitioner, and the sign language interpreter will only learn the group to which the participant belongs when the envelope is opened upon entering the medical consultation.

### Primary Outcomes

The primary outcome measure will be an assessment of communication using the DPC. The DPC [25] is made up of 13 questions. Each question has 4 response options, which are no, possibly no, possibly yes, and yes. The scale has high internal consistency (Cronbach α=.89) and good external validity. This is an easy-to-use and validated generic questionnaire to assess communication in the context of acute conditions, usable both in clinical research and in routine practice, which measures (1) creating a good interpersonal relationship, (2) exchanging information, and (3) making treatment-related decisions that involve the patients in decision-making. This scale was translated into Colombian Sign Language following a rigorous cultural adaptation and translation procedure [26]. The videos are hosted on the LimeSurvey platform in Colombian Sign Language, written in Spanish, and played on a tablet. The participants complete the DPC scale once they leave the medical consultation.

### Secondary Outcomes

The database contains clinical variables such as age, sex, place of birth, BMI, blood pressure, heart rate, respiratory rate, personal medical history (hypertension, diabetes, alcohol consumption, tobacco, and physical activity), use of hearing aids, questions on mental health, presence of hypertension, obesity, and cardiopulmonary, musculoskeletal, and metabolic disorders, recommendations provided by the doctor during a general medicine appointment, and so on. We will compute associations.

### Analyses

The participant demographics will be described both by group and overall sample. Responses for the scale were combined into 2 nominal categories (“yes, probably yes/no, probably no).

We will compute associations among the variables, such as the presence of different disorders, mental health of patients, current lifestyle, and past medical history, for both the groups, using both classic statistical methods (using the Fisher exact test) and machine learning (ML) algorithms, such as association rule learning, and then we will draw a comparison between these two approaches. We will also build suitable ML models (for instance, a regression model depicted below) to predict the occurrence of hypertension, obesity, and cardiopulmonary, musculoskeletal, and metabolic disorders based on the patient’s medical history (hypertension, diabetes, alcohol consumption, tobacco, and physical activity), place of birth, BMI, blood pressure, heart rate, respiratory rate, use of hearing aids, mental health and so on, for both the groups.

Response =predictor+age+gender+place of birth

where “predictor” denotes the patient’s medical history (hypertension, diabetes, alcohol consumption, tobacco, and physical activity), body mass index, blood pressure, heart rate, respiratory rate, use of hearing aids, mental health, and so on; and “response” denotes the occurrence of hypertension, obesity, and cardiopulmonary, musculoskeletal, and metabolic-disorders and so on.

We will report the odds ratios obtained from the regression model, as they are widely used to compare two groups. We will report the predictor-wise odds ratios obtained using the equation given below:

ORs = exp(coefficient of predictor)

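### The disorder models have no term for trial arm, so their odds ratios cannot compare the two groups, and fitting them by arm halves the sample

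*Protocol article*

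**What the plan says.** Three statements in the protocol article matter.

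- **Analyses, first paragraph.** Demographics are to be described by group and for the whole sample.
- **Analyses, associations and models.** "We will compute associations among the variables, such as the presence of different disorders, mental health of patients, current lifestyle, and past medical history, for" (the sentence goes on to name both groups), by Fisher's exact test and by machine-learning methods such as association rules. The next sentence plans prediction models, again for both groups and with no mention of the whole sample. The printed model regresses a response on a predictor, age, gender and place of birth. The named responses are hypertension, obesity, and cardiopulmonary, musculoskeletal and metabolic disorders. The named predictors are five history items, body mass index, blood pressure, heart rate, respiratory rate, hearing aid use and mental health. Both lists are left open.
- **Analyses, odds ratios.** The reason given for reporting odds ratios is that they are commonly used to compare two groups. Then: "We will report the predictor-wise odds ratios obtained using the equation given below", namely the exponential of the predictor's coefficient.

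The variables come from Secondary Outcomes, which ends: "recommendations provided by the doctor during a general medicine appointment, and so on. We will compute associations".

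**The concern.** The stated purpose and the stated model do not match. If the odds ratios are meant to compare the trial groups, the model needs a term that distinguishes them, and it has none. The exponential of the predictor coefficient compares patients with and without a characteristic, such as smokers and non-smokers. It says nothing about VRI against standard communication.

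If the models are fitted once per arm, the only route to a comparison is to set two within-arm results side by side. That is not a test of a difference. An association that appears in one arm and not in the other could be read as an effect of VRI when it reflects the small sample in each arm. Splitting also costs precision in every association.

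**Working it through.** **1. Sample available (Sample Size section).** The inputs are Zα=1.64, Zβ=0.84, p1=0.85, p2=0.65, margin 0.05, equal groups and 10% dropout.

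n = (1.64+0.84)² × [0.85×0.15 + 0.65×0.35] / (0.20−0.05)² = 6.1504 × 0.355 / 0.0225 = 97.04 per group.

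Total = 2 × 97.04 / 0.90 = 215.6, so 216. The plan's figures reproduce. About 97 are analysable per arm and 194 pooled.

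**2. What the model can estimate.** With response = predictor + age + gender + place of birth, there are two ways to fit it:
- By arm: two predictor odds ratios and no test of their difference.
- Pooled: one predictor odds ratio that ignores arm.

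Neither contains a VRI-versus-standard contrast.

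**3. Cost of splitting.** Assumptions that the document does not give: 25% exposed, 25% outcome among the unexposed, two-sided 5%, 80% power, no covariates. The Wald condition is ln(OR)/SE = 1.96 + 0.84 = 2.80, where SE² is the sum of the reciprocals of the four expected cell counts.

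- *n=97, OR=3.96.* Outcome risk in the exposed = 3.96×0.25/(0.75+3.96×0.25) = 0.569. Cells 13.8, 10.5, 18.2, 54.6. SE² = 0.0725+0.0957+0.0550+0.0183 = 0.2415, SE = 0.491. ln(3.96)/0.491 = 1.376/0.491 = 2.80.
- *n=194, OR=2.63.* Risk in the exposed = 0.467. Cells 22.7, 25.8, 36.4, 109.1. SE² = 0.1195, SE = 0.346. 0.967/0.346 = 2.80.

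So about 4.0 by arm against about 2.6 pooled. If 25% is instead taken as the overall outcome rate, the same condition gives about 4.2 and 2.7.

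**4. How often one arm only is expected by chance.** Suppose the odds ratio is truly 2.63 in both arms, which the pooled analysis detects with 80% power. Within one arm SE = 0.346 × √2 = 0.489, so z = 0.967/0.489 = 1.98 and power = Φ(1.98−1.96) = 0.51. The chance that exactly one arm reaches significance is 2 × 0.51 × 0.49 = 0.50. At a common odds ratio of 3.96 it is 2 × 0.80 × 0.20 = 0.32.

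**5. Chance findings if the whole grid were tested.** 5 × 11 = 55 named pairs. Removing hypertension with its own history, hypertension with blood pressure, and obesity with body mass index leaves 52, or 104 by arm. Assume that every null is true and that each pair gets a Fisher test at 5%. Fisher's actual size at 97 to 108 patients is mostly 0.02 to 0.04, so by arm 104×0.02 to 104×0.04 = 2.1 to 4.2. Simulated Fisher tests at assumed prevalences of 15% and 25% gave about 2.6 to 3.8 by arm and 1.7 to 2.3 pooled. If a quarter or a half of the associations are real, multiply by 0.75 or 0.5.

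**The case against.** **The phrase about both groups may not mean separate fits.** This stands in part. It could mean data covering both groups. The per-arm reading is the more natural one, because the same section adds the overall sample for demographics and does not for associations. The missing arm term is a defect of the stated rationale on either reading.

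**The two groups compared by an odds ratio might be exposed and unexposed patients.** Then the sentence would be a general remark and true. But the article uses the word groups for the trial arms throughout, so the sentence at least needs rewording.

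**Arm-specific results may be wanted.** History is taken during the consultation, so the way of communicating could affect what is recorded. That is a fair reason to look for differences between arms, and it calls for an interaction test.

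**A stronger reading is tempting:** that the plan runs about 100 tests at full alpha with no error control, so several reported associations will be false. The document does not support it:
- The only error level is in Sample Size ("considering the level of significance to be 5%, α =.05"). It is one-sided (z=1.64) and serves to size the superiority comparison. No level or decision rule is set for the associations.
- The 5 × 11 grid belongs to the regression sentence. The Fisher sentence names disorders, mental health, lifestyle and past history, not heart rate, respiratory rate, body mass index or hearing aids.
- A multiplicity policy or an exploratory label is commonly left to the full protocol or statistical analysis plan, which is not shown.

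**Conclusion.** The point holds in a limited form. The printed model cannot compare the arms, although its odds ratios are justified in those terms. On the per-arm reading each association uses half the sample, which raises the detectable odds ratio from about 2.6 to about 4.0. An association of equal strength in both arms would then reach significance in only one of them about a third to a half of the time. These sizes rest on the assumed 25% exposure and outcome rates and on a two-sided 5% level that the document does not set for this family.

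The count of chance findings (about 2 to 4 by arm, about 2 pooled) is an all-null illustration for a fully tested grid, not a forecast of what the trial will report. The associations concern patient characteristics, and the error rate of the primary DPC comparison is untouched. The change is worth making because it is simple and nearly free.

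**What to change.** In the Analyses section:

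1. Replace the model by response = predictor + arm + age + gender + place of birth, fitted once for each association on both arms together.
2. If a difference between arms is of interest, add an arm-by-predictor interaction and report its estimate and interval. Do not compare two within-arm results.
3. Delete or correct the rationale for the odds ratios, and say that each one compares levels of the predictor, adjusted for arm.

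Optional: label this family exploratory, state how many associations were examined, and give false-discovery-rate adjusted p-values.

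The cost is some wording and a few lines of code, with no new data. Fewer arm-specific associations will be reported. Interaction tests will also be imprecise: with the per-arm SE of 0.491, the SE of the difference is about 0.491 × √2 = 0.69. The detectable ratio of odds ratios is then about exp(2.80 × 0.69), or about 7. That imprecision is already present in any by-arm comparison, and the interaction test makes it visible.

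### The disorder models set hypertension against its own history and blood pressure, and obesity against BMI, so the odds ratios for these pairs are largely definitional

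*Protocol article*

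**What the plan says.** The Analyses section of the protocol article plans models "to predict the occurrence of hypertension, obesity, and cardiopulmonary, musculoskeletal, and metabolic disorders based on the" patient's history and measurements, for both randomised groups. It writes out one equation as an example: "Response =predictor+age+gender+place of birth".

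It then defines the two generic terms. The predictor stands for "medical history (hypertension, diabetes, alcohol consumption, tobacco, and physical activity), body mass index, blood pressure, heart rate, respiratory rate", and further for hearing-aid use, mental health and other unnamed items. The response "denotes the occurrence of hypertension, obesity, and cardiopulmonary, musculoskeletal, and metabolic-disorders and so on". No predictor is set aside for any response.

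The reported quantity is fixed as well: "We will report the predictor-wise odds ratios obtained using the equation given below", namely "ORs = exp(coefficient of predictor)".

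The Secondary Outcomes section places age, sex, BMI, blood pressure and medical history in the same database as "questions on mental health, presence of hypertension, obesity, and cardiopulmonary, musculoskeletal, and metabolic disorders". It does not say how any of these disorders is defined.

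**The concern.** Some variables stand on both sides of the model. Hypertension is named as a history item among the predictors and again as a response. Blood pressure and BMI are the measurements from which hypertension and obesity are ordinarily recognised. History of diabetes would duplicate part of the metabolic response if that category includes diabetes.

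An odds ratio from such a pair says nothing about risk. It either does not exist or shows how closely two entries in the same record agree. Reported among the other predictor-wise odds ratios, it could be read as a strong risk factor. It would also blur the planned comparison of classical tests with machine-learning methods, because both would recover the same definitional link wherever these variables are entered.

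A second, smaller issue is the wording. The models are described as predicting occurrence, but the data come from one appointment.

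**Working it through.** **1. Affected pairs.** The Analyses section names 11 predictors (history of hypertension, diabetes, alcohol, tobacco and physical activity; BMI; blood pressure; heart rate; respiratory rate; hearing-aid use; mental health) and 5 responses. That makes 11 × 5 = 55 pairs.

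| Response | Predictor | Relation |
|---|---|---|
| Hypertension | History of hypertension | Same condition named on both sides |
| Hypertension | Blood pressure | Measurement that ordinarily underlies the diagnosis |
| Obesity | BMI | Measurement that ordinarily underlies the diagnosis |
| Metabolic disorders | History of diabetes | Duplicate only if the category includes diabetes |

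This gives three pairs in two responses, or four pairs in three responses if diabetes counts as a metabolic disorder.

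**2. Timing.** The Intervention Group and Primary Outcomes sections describe one consultation followed by the communication scale. The Secondary Outcomes section records disorders, measurements and history in one database. No later onset is observed, so nothing is predicted forward in time.

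**3. Numbers available.** The point disputes no stated figure; the sample size only fixes N. The Sample Size section reproduces: (1.64 + 0.84)² × (0.85×0.15 + 0.65×0.35) / (0.20 − 0.05)² = 6.1504 × 0.355 / 0.0225 = 97.04 per group, and 2 × 97 / 0.90 = 215.6, about 216. "This study includes 216 participants who were randomized into 2 groups", hence 216 / 2 = 108 per group.

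The article gives no definitions or prevalences, so every input in steps 4 to 6 is an illustrative assumption.

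**4. Disorder coded strictly by a threshold.**
- Obesity taken as BMI of 30 or more, with BMI mean/SD of 25/4, 26.5/4.5 or 28/5: complete separation in 100% of 500 simulated samples per setting, at N = 108 and at N = 216.
- In an example fit adjusted for age and sex (N = 216, mean 26.5, SD 4.5), the BMI coefficient was 2.2, 20, 78, 142, 207 and 271 after 5, 10, 15, 20, 25 and 30 iterations. It does not converge, and its exponential has no finite value.
- Hypertension taken as systolic pressure of 140 or more (mean 122, SD 15, N = 216), related to systolic pressure: separation in 100% of 300 samples.

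**5. Obesity coded with some discordance from BMI.** With coding error equivalent to an SD of 0.5, 1 or 2 BMI units (mean 26.5, SD 4.5, N = 216), a fit was obtained in 98%, 100% and 100% of 300 samples. The median odds ratio per BMI unit was 44, 6.4 and 2.4. Only the coding error differs between these settings, so the size of the odds ratio is set by the coding.

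**6. Hypertension on history of hypertension.** Assume 20% have a history.
- Everyone with a history is coded hypertensive: a zero cell in 100% of samples and an infinite odds ratio.
- 90% with a history and 5% without are coded hypertensive: (0.90/0.10) / (0.05/0.95) = 9 × 19 = 171. A zero cell occurs in about 11% of samples at N = 108 and 1.5% at N = 216.
- 80% against 10%: (0.80/0.20) / (0.10/0.90) = 4 × 9 = 36.

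**7. Joint or one-at-a-time fitting.** The equation has a single predictor slot plus age, gender and place of birth. Entering candidates one at a time still produces hypertension on its history, hypertension on blood pressure and obesity on BMI. Entering them jointly keeps the same terms. Neither reading removes the circular pairs.

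**The case against.** The strongest reply is that the text is looser than a fixed model. The regression is offered as an example, the equation has one generic slot, and the list may be a pool of candidates. A reader might infer that the plan puts every predictor into every model. The article does not say so. That part of the reply stands, but step 7 shows that the looser reading does not cure the problem.

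A reader might also infer that these odds ratios cannot be estimated at all. The documents do not support that. They define none of the disorders, and they record the presence of hypertension and obesity separately from blood pressure and BMI, which is compatible with a clinician's diagnosis. Non-estimability holds only under strict threshold coding.

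The pairs also differ in strength. Literal duplication occurs once, for hypertension and its history. A single blood pressure reading need not match a recorded diagnosis, for example in a treated patient. The diabetes pair depends on a category that is not defined.

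The variables named for the Fisher tests and association rules are disorders, mental health, lifestyle and past history. BMI and blood pressure are not named there, although the list is only illustrative. For those methods the clear overlap is hypertension with its history. Excellent accuracy of the machine-learning models might be expected as well, but it was not computed.

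Finally, definitions and per-model variable sets are often left to a full protocol or analysis plan, which is not shown. That would answer an omission. Here the article itself states the responses, the predictors, the equation and the reported measure.

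**Conclusion.** The circularity stands as written. For hypertension with its history, hypertension with blood pressure, and obesity with BMI, the planned odds ratios are largely definitional. The same holds for metabolic disorders with history of diabetes if diabetes belongs to that category. Depending on how the disorders are coded, the result is either no finite odds ratio or a finite one that mainly measures agreement between two recordings of the same condition. The sizes shown (171 and 36 for hypertension; 44 down to 2.4 per BMI unit for obesity) rest on assumed prevalences, cut-offs and discordance. They show the mechanism and do not forecast the trial's results.

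The remaining 51 or 52 pairs are not in question; tobacco with cardiopulmonary disorders, for example, is not circular. It would be wrong to infer that the trial's main conclusion is at risk. The point is confined to secondary, exploratory models and does not touch the doctor-patient communication outcome, the randomised comparison or the sample size.

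**What to change.** In the Analyses section:

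- State how each disorder is defined and from which source it is coded.
- For each response, exclude the predictors that define or duplicate it: history of hypertension and blood pressure for hypertension; BMI for obesity; history of diabetes for metabolic disorders if diabetes is included.
- Exclude the same pairs from the association rules and Fisher tests wherever those variables are entered.
- Describe all results as cross-sectional associations and drop the language of predicting occurrence.

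The cost is a few excluded terms and some rewording. No new data are needed, and the non-circular pairs stay in the analysis.
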